## Abstract

**Background:**

The increasing development and spread of artificial and assistive intelligence is opening up new areas of application not only in applied medicine but also in related fields such as continuing medical education (CME), which is part of the mandatory training program for medical doctors in Germany. This study aimed to determine whether medical laypersons can successfully conduct training courses specifically for physicians with the help of a large language model (LLM) such as ChatGPT-4. This study aims to qualitatively and quantitatively investigate the impact of using artificial intelligence (AI; specifically ChatGPT) on the acquisition of credit points in German postgraduate medical education.

**Objective:**

Using this approach, we wanted to test further possible applications of AI in the postgraduate medical education setting and obtain results for practical use. Depending on the results, the potential influence of LLMs such as ChatGPT-4 on CME will be discussed, for example, as part of a SWOT (strengths, weaknesses, opportunities, threats) analysis.

**Methods:**

We designed a randomized controlled trial, in which adult high school students attempt to solve CME tests across six medical specialties in three study arms in total with 18 CME training courses per study arm under different interventional conditions with varying amounts of permitted use of ChatGPT-4. Sample size calculation was performed including guess probability (20% correct answers, SD=40%; confidence level of 1–α=.95/α=.05; test power of 1–β=.95; *P*<.05). The study was registered at open scientific framework.

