### Data Analysis

Sample size calculation was performed for the hypothesis that CME test results will improve from guess probability (20% correct answers, SD= 40%) to pass level (70% correct answers) with a confidence level of 1–α=.95, that is, α=.05, and a test power of 1–β=.95. Therefore, for an independent-samples, two-sided study, a sample size of at least 18 CME training courses per study arm is needed. Nonetheless, since the CME courses, as our study subjects, can be processed repeatedly using different methods without altering them or the methods, a paired-sample study is possible and preferable. This allows the same CME courses to be used in the three study arms. Although a sample size of 9 for a single-sided paired-sample study would be sufficient (only an improvement in CME test results is expected and desired by applying the study arm methods), we decided to take a conservative route and will work with 18 CME tests that will be run through all three study arms. The CME tests treated were randomly chosen from a large number of available tests. Care was taken to ensure that every high school student completed the same number of tests in each arm of the study so that confounding variables in the students were evenly distributed across the three groups. In addition, none of them would work on a single CME test twice using different methods to avoid learning effects. Together with the reuse of the CME tests in the three study arms (paired study, see above), these measures prevent any bias arising from the high school students as performing tools or the CME tests themselves as study participants. The AI-supported arms would run through within the shortest possible time and in the correct order so that unwanted training of the AI or the students during the process could be ruled out as much as possible. Statistical data analysis will be performed using the open-source software “R” (R Core Team; 2023). The data is presented as mean ± SD. Since the aim of the study is to identify differences in the percentage test results due to the different approaches in the three study arms, the Student *t* test (1-tailed) or the Mann-Whitney *U* test will be used for the pairwise comparison of means between groups, depending on the normality of the datasets. The Shapiro-Wilk test will be used to check normality. Fisher’s exact test was used to assess the independence of categorical variables. Benjamini-Hochberg adjustments of *P* values will be applied in multiple comparisons. Values of *P*<.05 were considered statistically significant.

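### The 40% SD behind the sample size equals that of one guessed question, not of a course score, so the stated need for at least 18 courses per arm does not follow; the error is conservative

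*Protocol article*

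**What the plan says.** Data Analysis in the protocol article sets up the calculation as a rise in test results from "guess probability (20% correct answers, SD= 40%) to pass level (70% correct answers". It fixes alpha at 0.05 and power at 0.95. Its conclusion reads: "for an independent-samples, two-sided study, a sample size of at least 18 CME training courses per study arm is needed".

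The section then prefers a paired design, in which the same courses go through all three arms. It adds: "Although a sample size of 9 for a single-sided paired-sample study would be sufficient". The trial nevertheless keeps 18 tests, which the article describes as the cautious choice. The abstract (Methods) repeats the inputs in short form: "Sample size calculation was performed including guess probability (20% correct answers, SD=40" (per cent). Alpha and power are the same there.

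Study Participants makes the CME course test, not the student, the object of study. Data Analysis makes the percentage test result the outcome. The descriptions of the three arms speak of questions in the plural. The number of questions per course is not given, and no source for the 40% is stated beyond its attachment to the guess probability.

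**The concern.** The sample size is counted in courses, so the SD in the calculation should describe how course percentage scores vary. The figure used is the SD of one right/wrong answer at a 20% guess rate. Averaging over the questions of a course shrinks that SD, so a question-level SD has been paired with a course-level n.

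What is at stake is the rationale, not the safety of the design. As printed, the calculation tells the reader that 18 courses are the minimum for a 50-point difference and, by implication, that about 50 points is all 18 courses could detect. Neither describes the outcome that will be analysed. This matters for the contrast between the two ChatGPT arms. The Discussion wants to know whether supplying the course text gives better results, and that difference may be well below 50 points.

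**Working it through.** **Inputs from Data Analysis.** Guessing mean 20%, pass level 70%, SD 40%, alpha 0.05, power 0.95. Difference = 70 - 20 = 50 points. Standardised difference d = 50/40 = 1.25.

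**Step 1: reproduce the stated figures** (t test, noncentral t distribution).

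- Independent samples, two-sided: power is 0.942 at n = 17 and 0.954 at n = 18 per arm, so 18.
- Paired, one-sided, with 40 as the SD of the difference: power is 0.936 at n = 8 and 0.961 at n = 9, so 9.

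Both match the article. The arithmetic is right, and it shows that 40% was entered as the SD of a course score and again as the SD of the within-course difference.

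**Step 2: what 40% is.** For one question guessed at p = 0.2, SD = sqrt(p(1 - p)) = sqrt(0.2 x 0.8) = 0.400. For any score confined to 0-100% with mean 20%, the variance cannot exceed 0.2 x 0.8 = 0.16. So 40% is also the upper limit, reached only if every course scores either 0% or 100%. For k independently guessed questions, SD = 40/sqrt(k), which is below 40 for every k above 1.

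**Step 3: repeat the independent two-sided calculation with a course-level SD.** The article does not give k, so 5, 10 and 20 are assumptions. The pooled SD averages the binomial variances at 20% and 70%: sqrt((0.16 + 0.21)/(2k)).

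| Questions per course (assumed) | SD under guessing | n per arm | Pooled SD | n per arm |
|---|---|---|---|---|
| 5 | 17.9 | 5 | 19.2 | 6 |
| 10 | 12.6 | 4 | 13.6 | 4 |
| 20 | 8.9 | 3 | 9.6 | 3 |

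**Step 4: allow for courses of differing difficulty.** Real course scores will vary by more than the binomial part. With an assumed total SD:

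| Total SD (assumed) | d | n per arm |
|---|---|---|
| 20 | 2.50 | 6 |
| 25 | 2.00 | 8 |
| 30 | 1.67 | 11 |
| 40 (as in the article) | 1.25 | 18 |

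**Step 5: what 18 paired tests can detect with 95% power.** At n = 18 the paired t test needs a difference of 0.809 SDs one-sided or 0.902 two-sided, where the SD is that of the within-course difference. With that SD assumed to be 20-25 points:

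- one-sided: 0.809 x 20 = 16.2 to 0.809 x 25 = 20.2 points;
- two-sided: 0.902 x 20 = 18.0 to 0.902 x 25 = 22.6 points.

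The article's own inputs (SD 40, independent, two-sided, n = 18) imply about 49.5 points.

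**The case against.** The strongest reply is that nothing in the design changes. A smaller SD makes 18 courses more than enough for 20% versus 70%, and the authors already took 18 where they thought 9 would do. This stands, and it is why the point is minor. What remains is a printed requirement that the stated hypothesis does not produce.

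A second reply is that the article never says how 40% was obtained, so it could be a deliberate worst case, being the maximum SD at a mean of 20%. That is numerically possible. But the article does not present it as a bound; it gives it as the SD belonging to the guess rate, and it then says at least 18 courses are needed. A worst-case SD would support saying that 18 suffice, not that fewer would fail.

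A third is that an article may leave the number of questions per test to the full protocol. That is fair, and its absence is not the fault here. The fault is an SD, printed in full, that does not belong to the unit being counted.

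Three stronger readings are tempting and should be resisted:

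- **That 3-6 courses would really have been enough.** This holds only if all courses are equally difficult. With six specialties and three publishers that is unlikely, so the range has to extend to about 11 at an SD of 30.
- **That the trial is underpowered.** For the stated hypothesis it is not.
- **That the paired 9 exposes a power problem.** Using 40 both for each score and for the difference implies a within-course correlation of 0.5, which the article does not state. But the trial does not run with 9. Even with SD 40 and zero correlation (SD of the difference 40 x sqrt(2) = 56.6), 18 pairs give 97% power for 50 points one-sided and 94% two-sided.

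**Conclusion.** The concern holds as a minor error in the sample size justification. The 40% SD equals that of a single guessed question and cannot be the guessing SD of a course with several independently guessed questions. The statement that at least 18 courses per arm are needed therefore does not follow from the hypothesis, and neither does the paired 9, which reuses 40 as the SD of the difference.

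The direction is conservative. In place of 18, the same independent two-sided calculation gives about 3-6 per arm under pure guessing variation, or about 6-11 at a total SD of 20-30. These figures rest on assumed question counts and SDs, because the article gives neither. That 40% is too large for a guessed multi-question score needs no such assumption. The documents support neither a claim that the number of tests is inadequate nor a claim that it should be cut.

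**What to change.** Keep the 18 tests; Results reports that five of the six students have already been tested. In Data Analysis, and correspondingly in the abstract:

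- replace the 40% with a justified SD of the course percentage score and a justified SD of the within-course difference, giving the number of questions per test where the SD is derived from it;
- drop the claim that at least 18 courses per arm are needed, and the paired figure of 9 built on the same input;
- present 18 as the chosen number and state the difference that 18 paired tests can detect with 95% power. As an illustration, this is about 16-20 points one-sided (the article plans a one-tailed t test) or 18-23 points two-sided, if the SD of the paired difference is 20-25 points (assumed).

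The cost is one recalculation and about two sentences, with no new data and no change to the number of tests.

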**Results:**

As of October 2024, the acquisition of data and students to participate in the trial is ongoing. Upon analysis of our acquired data, we predict our findings to be ready for publication as soon as early 2025.

**Conclusions:**

We aim to prove that the advances in AI, especially LLMs such as ChatGPT-4 have considerable effects on medical laypersons’ ability to successfully pass CME tests. The implications that this holds on how the concept of continuous medical education requires reevaluation are yet to be contemplated.

**Trial Registration:**

OSF Registries 10.17605/OSF.IO/MZNUF; https://osf.io/mznuf

**International Registered Report Identifier (IRRID):**

PRR1-10.2196/63887

## Introduction

ChatGPT-4 is the latest development in the large language model (LLM) family from ChatGPT. It is said to be trained on more than one trillion parameters, making it one of the most advanced LLMs currently available for generating conversation-style responses to user input. The parameters are the numerical values that determine how a neural network processes input data and produces output data. They are learned from data during the training process, encoding the model’s knowledge and skills [1].

Since its launch by OpenAI, the ChatGPT family has stimulated widespread conversation and momentum across different specialties in medicine, as demonstrated by more than 3300 publications related to ChatGPT (or Chat-GPT) indexed in PubMed as of mid-May 2024. Generally, LLMs enable humans to interact and discuss a broad range of topics with artificial intelligence (AI) chatbots. New features of ChatGPT-4 include the acceptance of images as input and the generation of captions, classifications, and analyses, which were not available in earlier versions. Compared to its predecessors, ChatGPT-4 is 82% less likely to respond to inappropriate content requests and 40% more likely to provide factual answers than GPT-3 in internal evaluations [2].

After its success in passing the United States Medical Licensing Examination, performing at a level comparable to that of a third-year medical student [3], these results have been largely confirmed across various medical specialties. Comparisons with different ChatGPT versions and other LLM providers, such as Google, support these findings [3-13]. There are currently two reviews on this topic [14,15], and recent data specific to Germany have been published [16].

In conclusion, there is now a range of data on the use of LLMs in undergraduate education and teaching but less on postgraduate education, such as continuing medical education (CME) [17] or self-assessment programs [4]. Table 1 shows a selection of studies on this topic.

In Germany, CME, which is mandatory for medical specialists, requires earning 250 training points over five years. These CME points can be acquired through further specialization, attending congresses and conferences, and studying medical literature with consecutive answers to specific questions in the text. This approach essentially “credits” the self-study time spent attentively reading a text and then answering questions.

For this study, we decided to use ChatGPT-4 because of its extensive database and ability to enter texts directly. Additionally, the input and operation of ChatGPT are carried out by adult high school students without any prior medical training. This was to differentiate as clearly as possible whether and to what extent LLMs can offer support today. This study aims to provide further insight into whether AI, in the form of LLMs, can support various levels of medical education by correctly answering CME-relevant questions, allowing participants to generate CME credits independently of existing medical knowledge.

**Table 1 table1:** Data on ChatGPT and postgraduate medical education (continuing medical education or self-assessment programs).

First author	Year	Study	Comparator	Major findings	Conclusions
Sherazi and Canes [4]	2023	Comparative trial	ChatGPT-3.5 versus ChatGPT-4	GPT-4 scored significantly higher than GPT-3.5 on the AUA^a^ SASP^b^ examinations in overall performance, across all test years, and in various urology topic areas.	Results suggest improvement in evolving AI^c^ LLM^d^ in answering clinical urology questions. Certain aspects of medical knowledge and clinical reasoning remain challenging for LLM.
Riedel et al [16]	2023	Comparative trial	Performance of ChatGPT on OB/GYN^e^ course examinations versus questions from the German medical state licensing examinations	ChatGPT demonstrated consistent and comparable performance across both datasets, providing correct responses at a rate comparable with that of medical students.	ChatGPT has promise as a supplementary tool in medical education and clinical practice, providing efficient and personalized learning experiences and assistance for health care providers.
Noda et al [18]	2024	Comparative trial	ChatGPT-3.5 versus ChatGPT-4 versus Bard (Gemini)	GPT-3.5 and Bard performed similarly while being significantly surpassed by GPT-4. GPT-4’s performance was between third- and fourth-year nephrology residents.	GPT-4 outperformed GPT-3.5 and Bard, meeting the Nephrology Board renewal standards in specific years, albeit marginally. The results highlight LLMs potential and limitations.
Ali et al [6]	2023	Comparative trial	ChatGPT-3.5 versus ChatGPT-4 versus user average	GPT-4 significantly outperformed question bank users and GPT-3.5. Increased word count and higher-order problem-solving were associated with lower accuracy for GPT-3.5 not however for GPT-4.	LLMs achieved passing scores on a mock 500-question neurosurgical written board examination, with GPT-4 significantly outperforming ChatGPT.
Watari et al [13]	2023	Comparison study	Chat GPT-4 versus Japanese Residents’ performance on GM-ITE^f^	Of 137 GM-ITE questions in Japanese, GPT-4 scores were significantly higher than the mean scores of residents.	GPT-4 demonstrated a tendency to score higher on difficult questions. However, GPT-4 scored comparatively lower on questions testing attitudes toward patients and professionalism requiring an understanding of context and communication.
Guerra et al [5]	2023	Comparative trial	ChatGPT-4 versus ChatGPT, SANS^g^ users, medical students, and neurosurgery residents	GPT-4 outperformed ChatGPT exceeding the performances of medical students, neurosurgery residents, and the national average of SANS users across all categories.	GPT-4 significantly outperformed medical students, neurosurgery residents, and the national average of SANS users.

^a^AUA: American Urological Association.

^b^SASP: self-assessment study program.

^c^AI: artificial intelligence.

^d^LLM: large language model.

^e^OB/GYN: obstetrics and gynecology.

^f^GM-ITE: General Medicine In-Training Examination.

^g^SANS: self-assessment in neurosurgery examination.

## Methods

### Study Design

This is a randomized controlled trial that will be undertaken following the Declaration of Helsinki principles and after approval by the local Ethics Committee of Witten/Herdecke University (S-108/2024, date of approval May 15, 2024) and after registration in a study register (open scientific framework). To obtain representative, comprehensive, and meaningful data, three large German publishing houses (Deutscher Ärzteverlag GmbH, Cologne; Georg Thieme Verlag KG, Stuttgart; and Springer Medizin Verlag, Heidelberg) that offer journals with CME will be evaluated for one volume each of already expired journals (ie, without the possibility of earning credit points) from the fields of internal medicine, surgery, gynecology, pediatrics, neurology, and anesthesiology. The CME tests provided by the publishing houses needed no further adaptation for utilization in the study.

### Ethical Considerations

The study protocol which was submitted to and accepted by the Ethics Committee of University Witten/Herdecke (S-108/2024, date of approval May 15, 2024) stated decisively that no monetary or other compensation was to occur. The participant’s information was depersonalized by means of not collecting any personal information to begin with, as they were deemed insignificant to the study’s results leading to participants enrolling entirely voluntarily. Furthermore, to participate in the study, the students were required to provide a signed informed consent form which all students were given the opportunity to voice concerns and questions and were informed about their ability to revoke their consent without having to provide a reason, while not having to expect any repercussions.

### Study Participants

To minimize any influence from prior medical knowledge on the results, adult high school students from North Rhine-Westphalia who are willing to participate will be randomized into three study arms. As high school students can be assumed to be void of relevant medical prior education, the choice to include this group as participants is based on its ability to represent the approximate level of medical knowledge of the general population. The inclusion and exclusion criteria are shown in Textbox 1. It should be emphasized that it is not the high school students who are the participants of the study but the CME course tests to which the methods of the three study arms are applied. Careful considerations were put into the selection of the CME tests screening for images of diseases that students may have deemed disturbing. Such CMEs were excluded. The students were encouraged to voice concerns if the contents of the CME tests resulted in uneasiness. Furthermore, ample opportunity was provided for discussing the students’ experiences if deemed necessary by the participants. All these measures aided in minimizing the potential psychological impact of participation in the study. The experience of the participants while attempting to solve the CME tests is not represented in the study’s results as they were deemed to exceed the scope of the study. The student’s proficiency in the German language was required in the hope of avoiding skewed results based on linguistic incomprehension of the provided literature. The students act purely as “tools,” preferably without any medical knowledge of their own.

Inclusion and exclusion criteria.
**Inclusion criteria**
Aged 18 years or olderVoluntary participationNo financial compensationGerman as a native language or at a native speaker levelAbility to operate ChatGPT or other required software
**Exclusion criteria**
Being underageRefusal to participateInsufficient German language skillsInability to operate ChatGPT or other required software

### Interventions

This trial is designed as a three-armed randomized controlled trial, including one control arm.

#### Intervention Group 1: “All-In”

In this group, CME-subject-specific text is entered into ChatGPT-4 first, and then, the questions are answered by ChatGPT based on that input.

#### Intervention Group 2: “Just Answers”

In this group, questions are answered using only the knowledge available in the ChatGPT-4 database at that time, without entering any subject-specific text first.

#### Control Group 3: “Search and Find”

Participants in this group were asked to answer the questions using only keywords and common sense without any AI support. As the CME were viewed as digital files, the use of “find in text” of the respective document viewing software was permitted.

The approach to having the CME test questions answered in three study arms aims to uncover significant differences in ChatGPT-4’s ability to solve the CME tests, as well as assess the varying time required in the individual study arms.

### Data Analysis

Sample size calculation was performed for the hypothesis that CME test results will improve from guess probability (20% correct answers, SD= 40%) to pass level (70% correct answers) with a confidence level of 1–α=.95, that is, α=.05, and a test power of 1–β=.95. Therefore, for an independent-samples, two-sided study, a sample size of at least 18 CME training courses per study arm is needed. Nonetheless, since the CME courses, as our study subjects, can be processed repeatedly using different methods without altering them or the methods, a paired-sample study is possible and preferable. This allows the same CME courses to be used in the three study arms. Although a sample size of 9 for a single-sided paired-sample study would be sufficient (only an improvement in CME test results is expected and desired by applying the study arm methods), we decided to take a conservative route and will work with 18 CME tests that will be run through all three study arms. The CME tests treated were randomly chosen from a large number of available tests. Care was taken to ensure that every high school student completed the same number of tests in each arm of the study so that confounding variables in the students were evenly distributed across the three groups. In addition, none of them would work on a single CME test twice using different methods to avoid learning effects. Together with the reuse of the CME tests in the three study arms (paired study, see above), these measures prevent any bias arising from the high school students as performing tools or the CME tests themselves as study participants. The AI-supported arms would run through within the shortest possible time and in the correct order so that unwanted training of the AI or the students during the process could be ruled out as much as possible. Statistical data analysis will be performed using the open-source software “R” (R Core Team; 2023). The data is presented as mean ± SD. Since the aim of the study is to identify differences in the percentage test results due to the different approaches in the three study arms, the Student *t* test (1-tailed) or the Mann-Whitney *U* test will be used for the pairwise comparison of means between groups, depending on the normality of the datasets. The Shapiro-Wilk test will be used to check normality. Fisher’s exact test was used to assess the independence of categorical variables. Benjamini-Hochberg adjustments of *P* values will be applied in multiple comparisons. Values of *P*<.05 were considered statistically significant.

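### The pairwise t tests are 1-tailed at .05, although the sample size is two-sided, the stated aim is non-directional, and the control could outscore an AI arm

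*Protocol article*

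**What the plan says.** All the elements except the arm descriptions stand in Data Analysis.

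- **Design basis.** The effect is an improvement from "guess probability (20% correct answers, SD= 40%) to pass level (70% correct answers"), with "that is, α=.05, and a test power of 1–β=.95". From this the article concludes that "for an independent-samples, two-sided study, a sample size of at least 18 CME training courses per study arm is needed".
- **Alternative considered.** Because the same CME courses can be used in every arm, the article says that "a sample size of 9 for a single-sided paired-sample study would be sufficient", on the ground that "only an improvement in CME test results is expected and desired by applying the study arm methods". It keeps the larger number: "we decided to take a conservative route and will work with 18 CME tests that will be run through all three study arms".
- **Analysis.** The aim is worded as identifying differences in percentage results between the three arms. The pairwise comparisons use a Student t test marked 1-tailed, or a Mann-Whitney U test with no sidedness given. The threshold is P<.05, with Benjamini-Hochberg adjustment. The section lists no direction for the individual pairs.
- **Arms.** Just Answers relies on what ChatGPT-4 already holds, with no course text entered. In Search and Find, the control, there is no AI, but "the use of “find in text” of the respective document viewing software was permitted".

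**The concern.** The sample size and the test use different standards of evidence. The two-sided calculation allows 2.5% in each tail; the 1-tailed test allows 5% in one.

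The reason given for one tail is also a weak fit to the comparisons being made. The planning effect runs from guessing to pass level, and guessing is not one of the arms. The tests compare arms with one another. For All-In against Just Answers, a direction is easy to infer. For Just Answers against Search and Find it is not: one arm has the model without the text, the other has the text without the model. That a result is desired is no statistical ground for excluding its opposite.

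At stake is what the trial can report. If laypersons with a search function outscore ChatGPT-4 without the text, that bears directly on the question posed in the Discussion, namely whether the course literature is needed for superior results. A 1-tailed test in favour of AI has no way to declare it.

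**Working it through.** **Inputs from Data Analysis.** Difference 70 − 20 = 50 points; SD 40; standardised effect d = 50/40 = 1.25; α = .05; power .95; n = 18.

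**1. Reproduce the plan's figures.**

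The normal approximation for two independent groups, two-sided, is n = 2(1.96 + 1.645)²/1.25² = 16.6, so 17 per arm. The exact calculation uses the noncentral t distribution with noncentrality d√(n/2) and 2n − 2 degrees of freedom. For the paired design the noncentrality is d√n with n − 1 degrees of freedom, taking SD 40 as the SD of the differences.

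| Design | Sides | Smallest n | Power at that n | Power at n − 1 |
|---|---|---|---|---|
| Independent | two | 18 | 95.4% | 94.2% |
| Independent | one | 15 | 95.5% | 94.2% |
| Paired | one | 9 | 96.1% | 93.6% |
| Paired | two | 11 | 96.1% | 93.9% |

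Both stated figures, 18 and 9, are confirmed. Sidedness alone moves the paired requirement from 9 to 11. The rest of the step to 18 comes from ignoring the pairing.

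**2. What the 1-tailed test changes.**

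| At n = 18 | Critical t, 1-tailed .05 | Critical t, two-sided .05 |
|---|---|---|
| Independent (34 df) | 1.691 | 2.032 |
| Paired (17 df) | 1.740 | 2.110 |

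At d = 1.25 the independent-samples power becomes 97.9% instead of 95.4%. The test is therefore looser than the one on which 18 was planned.

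**3. If the control is better.** The article gives no expected score per arm, so this step rests on assumptions: a control advantage of 15 points and a correlation of 0.5 between arms within a CME test. The SD of the differences is SD × √(2(1 − 0.5)) = SD. With n = 18, paired:

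| SD | d | d√18 | Two-sided power | 1-tailed test for AI superiority rejects |
|---|---|---|---|---|
| 40 (the plan's value) | 15/40 = 0.375 | 1.59 | 32% | below 0.1% |
| 20 (assumed) | 15/20 = 0.75 | 3.18 | 85% | about 0.0001% |

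The few 1-tailed rejections would point the wrong way, towards AI. The near-zero figures do not depend on the chosen inputs: any 1-tailed test is blind to an effect in the other tail.

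**4. Cost of testing two-sided.** At d = 1.25 and n = 18, two-sided power is 99.9% paired and 95.4% independent. The power target is met on either reading.

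**The case against.** The strongest defence is that the 1-tailed choice is disclosed and a reason is given. With the tail fixed in advance, a 1-tailed test at .05 has a 5% error for its own hypothesis, and preferring two-sided .05 or one-sided .025 is partly convention. This stands. What it does not do is reconcile the test with a non-directional aim and a two-sided sample size.

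Directions can also be inferred. The Discussion asks whether the literature was needed for superior results, which suggests All-In above Just Answers, and the aim of showing that AI lets laypersons pass suggests AI above control. A pair-by-pair list might stand in a fuller document. Even so, an inferred direction does not make a reversal impossible for Just Answers against Search and Find. In turn, that the control might win is itself an inference from the arm descriptions.

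Three stronger readings are tempting and go too far:

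- **That the error rate is really 10%.** This would follow only if the tail were chosen after seeing the means. The article does not say so, and its rationale points to a preset direction.
- **That 18 is called conservative merely because it is two-sided.** The article contrasts a single-sided paired design with a two-sided independent one, and most of the increase comes from the pairing.
- **That 85% power to detect a control advantage is being given up.** That figure needs an SD of 20. With the plan's SD of 40 and the other assumptions unchanged, it is 32%.

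**Conclusion.** The point holds as an inconsistency between the analysis and its own design basis, and should be fixed. The sample size is two-sided and the aim is to find differences, yet the t test is 1-tailed and the rank test's sidedness is open. The justification does not reach all three pairs.

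The firm part of its size is 5% in one tail against the planned 2.5%, together with no possibility of declaring a control advantage if the tail is set towards AI. How much detectable signal is lost (32% to 85% power in the illustration) depends on the assumed 15 points, correlation and SD. The sample size is sound, and Benjamini-Hochberg adjustment, which deals with multiplicity, does not bear on the choice of tail.

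**What to change.** In Data Analysis, replace the 1-tailed specification with two-sided tests at .05 for all three pairwise comparisons. Say the same of the rank test used when normality fails. Apply Benjamini-Hochberg to the two-sided P values, and remove the statement that only improvement is expected and desired as a justification for the choice of test.

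The cost is a wording change. P values from the t test in the expected direction double. No further CME tests are required, since 11 suffice for a two-sided paired comparison on the plan's inputs (SD 40 taken as the SD of the differences) and 18 are planned. The Results section of the article places the data analysis after the end of data collection, so the change could be made before any comparison is run.
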